### Assessment and blinding

It will not be possible to blind the clinicians administering the intervention.
Patients and research associates collecting outcome measures will be blinded to
treatment allocation. Patients with any outstanding postoperative cognitive
tests (typically either day 2 or day 7) after discharge from hospital
will have these administered by a trained research associate visiting them at
home or an agreed location. Patients will receive a follow-up telephone call at
6 weeks to record any VTEs since surgery. OKS, EQ-5D and complications
questionnaire will be posted to the patient at 6 and 12 months. We will
use techniques common in long-term cohort studies to ensure minimum loss to
follow-up, such as collection of next of kin contact addresses and telephone
numbers, mobile telephone numbers and email addresses. A maximum of three
attempts will be made acquire outcome data at each time point.

### Sample size calculation

As this is a pilot trial and not designed to measure effect, a formal sample size
calculation is not required (the statistical analysis will be largely
descriptive). We propose seeking to recruit and obtain primary clinical outcome
data for 50 patients for descriptive analysis.

### Data management

After baseline demographic data is collected, a unique trial number will identify
patients. All data collected will be entered into a secure trial database held
at Warwick Clinical Trials Unit (WCTU). Identifiable patient information will be
held in a locked filing cabinet and coded with a patient trial number. The WCTU
quality assurance manager will audit trial records in accordance with standard
operating procedures. Outcomes will not be analysed until all primary outcome
data are collected.

### Trial oversight

The Trial Management Group (TMG), consisting of the staff involved in the
day-to-day running of the study, will meet monthly. Significant issues arising
from management meetings will be referred to the Trial Steering
Committee (TSC) as appropriate. The trial will be guided by a TSC, a
group of respected and experienced personnel and trialists as well as lay
representatives. The TSC will have an independent chairperson. At least two
formal TSC meetings will be held—one before the trial starts and one
before recruitment to the trial completes. As this is a small feasibility study,
there will not be a data monitoring committee. AEs and serious AEs will
be monitored by the investigators. AEs will be assessed for causality within
24 hours of notification and patients followed up as per protocol. The
trial may be stopped prematurely if mandated by ethics committee, a major
unexpected safety concern arises or funding ceases. Any proposed changes to the
protocol will first be reviewed by the TSC and, if approved, it will be
submitted to the trial sponsor, funding body and local research ethics
committee. All approved protocols will be marked by a version number and date.
Requests for access to the final dataset will be overseen by the TSC. Reasonable
requests will then be given access to a full anonymised dataset.

## Integrated qualitative research study

### Method

#### Patients

In-depth semistructured interviews among with randomised patients and
potential patients who decline to take part in the pilot trial will help
understand people’s views regarding participation in the pilot trial.
A purposive sample of around 30 people (evenly split between recruited and
not recruited) will be interviewed, based on patient demographics (including
age, gender and socioeconomic status).^30 31^ Patients will be recruited by a trained research
associate and interviews will then be undertaken at a time convenient to the
patient.

#### Surgeons

A survey will be undertaken among surgeons who routinely do TKR surgery. The
survey will help gauge the extent to which this community is in clinical
equipoise and would be willing to engage with and support a larger trial. We
will use a web-based survey of members of the British Association for
Surgery of the Knee (BASK). BASK has a UK membership of over 100 practising
knee surgeons of whom the majority routinely undertake TKR surgery. A sample
of at least 20 BASK surgeons (both those clearly in equipoise and those that
are not) will be invited to take part in more in-depth qualitative
interviews. We will use the general theory of implementation to investigate
and understand the core constructs of sense-making processes of patients and
surgeons regarding the feasibility of a full trial and to help understand
any barriers and enablers for a larger trial.

Digital audio recordings of interviews will be transcribed verbatim, checked
and anonymised. Data will be managed and shared using NVivo analysis
software. The analysis will be informed by a constant comparative approach,
where early analysis informs subsequent data collection, and data analysis
takes place alongside data collection.^30^ This means insights from patients and surgeons can be
explored further in the ongoing interviews. Data are coded from the start of
data collection, and new data are compared with existing data. Codes are
compared; categories are constructed and explored to ensure they are robust
and then they are linked with relevant theoretical literature. A technique
of triangulation protocol will be used to facilitate the integration of the
findings of the qualitative research with the quantitative data, thereby
helping to determine the overall feasibility of a full trial.^32^ The data from patient interviews
will also be used to help design optimal patient information materials for a
larger trial.

## Multicentre cohort study

The National Joint Registry (NJR) is a population-based registry of joint
replacements in the UK and covers both the NHS and private sectors. From April 2003
to December 2003, the NJR collected data on the use of tourniquets for TKR surgery
in England and Wales. At this stage, there were 406 hospitals listed within the NJR
system (NHS hospitals, independent sector hospitals and treatment
centres—both NHS funded and privately funded) and of these, 384 returned data
(ie, 94%). The NJR dataset also contains many other key variables that are
known to affect mortality, implant survivorship (revision rate) and the risk of VTE
(1) use and type of VTE prophylaxis (such as low molecular weight heparin,
aspirin and intermittent calf pump), (2) type of implant used, (3) use of
cement and (4) basic patient demographics including age, body mass index
(BMI) and American Society of Anesthesiologists (ASA) grade.

### Method

We will access NJR data for the period in which tourniquet use was collected as
part of the minimum dataset standard for knee replacement surgery: April 2003 to
December 2003. We will analyse only data from primary cemented TKRs. Tourniquet
use along with other routinely collected NJR baseline variables—age at
time of surgery, sex and ASA classification—will be analysed to
measure for independent effects on all cause revision. A tourniquet will be
classed as used if even for a selective period of the procedure such as
cementation. Sociodemographics, comorbidities, VTEs, cerebrovascular accident
(CVAs or stroke) and length of hospital stay will be obtained by using patient
identifiers (NHS number, gender, date of birth, postcode, procedure code and
local patient identifier code) from the NJR to link the data to the Hospital
Episode Statistics (HES) database. The HES data will provide details of
VTE, sociodemographics, comorbidities and hospital length of stay for the TKR.
The study will specifically estimate differences between groups (tourniquet or
no tourniquet) for the following:baseline characteristics (age, BMI, ASA, comorbidities, type of VTE
prophylaxis, type of implant and sociodemographics)all-cause mortality up to 12 monthslength of inpatient hospital stayrisk of surgical complications up to 30 daysrisk of VTE up to 12 monthsrisk of CVA up to 12 monthsrisk of revision at 1, 5 and 10 years.

### Statistical Analysis

The Kaplan-Meier method will be used to calculate mortality and revision rates in
those who underwent TKR with and without a tourniquet. Multivariate logistic
regression will be used to assess the effect of age, BMI, socioeconomic status,
tourniquet use, type of VTE prophylaxis, ASA grade, comorbidities and type of
TKR implant (cemented or uncemented) on risk of VTE, CVA and risk of revision.
The results of these analyses will inform the planning of a subsequent
definitive full trial, if such a trial is feasible.

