## Introduction

Arthritis of the knee can cause pain and restrict activities of daily living. Total
knee replacement (TKR) surgery is a surgical procedure aimed at resolving the
symptoms of end-stage knee arthritis.^1^ TKR
surgery is typically undertaken with the aid of a tourniquet. A tourniquet acts as
an occlusive device around the thigh with the aim of reducing blood flow distally.
In the UK, over 90% of TKRs are performed with a tourniquet.^2 3^ Anecdotally, surgeons believe using a tourniquet provides
a bloodless field to improve the operative field of view.^4^ Many surgeons also believe using a tourniquet improves the
quality of the cementation of the knee implants^5^ by reducing bone bleeding and allowing better interdigitation of the
cement into the porous bone.

Previous systematic reviews have concluded that the use of tourniquets did not reduce
intraoperative or postoperative blood loss^6^
and were associated with significant complications including venous thromboembolic
events (VTEs),^5^ wound infection, bruising and
nerve palsy.^5 7^

In TKR surgery, a tourniquet causes both arterial and venous stasis for the duration
it is applied. It is therefore unsurprising that the use of a thigh tourniquet might
increase the risk of postoperative VTE.^2^
However, VTE may not be the only thromboembolic risk associated with using a
tourniquet. Research has demonstrated that systemic emboli can occur when the
tourniquet is deflated with up to a 60% prevalence of echogenic material in
the circle of Willis.^8 9^ Emboli may reach
the systemic circulation through the pulmonary capillaries or the opening of other
pulmonary vessels.^9^ The prevalence of
postoperative cognitive impairment after TKR is high with reports in the literature
varying from 41%–75% at 7 days to 18%–45% at 3 months,
and this may in part be explained by cerebral emboli if they are occurring following
the release of a tourniquet.^10^

Although studies have demonstrated that tourniquets do not substantially reduce blood
loss and may increase complications, a review of these studies, by Alcelik
*et al*
7, identified significant design flaws,
including issues with randomisation, blinding and the absence of clearly defined
outcome measures. Furthermore, no controlled studies have addressed or quantified
one of the most potentially serious risks associated with tourniquet, which are
cerebral emboli, and any resultant cognitive impairment.

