#### Exclusion criteria

Patients for whom MRI is contraindicated due to:non-compliant heart pacemaker or defibrillatornon-compliant metallic foreign body, for example, in one
or both eyes and aneurysm clips in the brainclaustrophobia (eg, difficulty in an elevator or
telephone box).Patients not suitable for a thigh tourniquet (eg, peripheral vascular
disease).Previous participation in the SAFE-TKR study.

Patients already scheduled for TKR surgery will be screened based on the
eligibility criteria. A trained research associate will contact potentially
eligible patients via telephone. Patients who are interested in taking part
in the study will then be sent a patient information sheet and consent form
and a date arranged to answer any further questions about the study and take
consent. Verbal consent will initially be taken, followed by signed written
consent via post or in person depending on the patient’s preference
(see online supplementary appendix 1 and 2).

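### In the registry cohort, 12-month mortality is left out of the adjusted analyses, and revision to 10 years is adjusted only by logistic regression with no stated rule for deaths

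*Protocol article*

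**What the plan says.** All of this is in the Protocol article, under Multicentre cohort study.

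- **Outcomes.** The Method section commits to estimating differences between the tourniquet groups in baseline characteristics, 12-month all-cause mortality, length of stay, 30-day complications, 12-month VTE, 12-month CVA, and revision at 1, 5 and 10 years. For revision it wants registry variables analysed to "measure for independent effects on all cause revision".
- **Unadjusted method.** The Statistical Analysis section opens: "The Kaplan-Meier method will be used to calculate mortality and revision rates in" patients operated on with and without a tourniquet. No covariates are mentioned.
- **Adjusted method.** Multivariate logistic "regression will be used to assess the effect of age, BMI, socioeconomic status" and further covariates, among them the tourniquet itself, thromboprophylaxis, ASA grade and comorbid conditions. The sentence ends with the last covariate and the outcomes: "TKR implant (cemented or uncemented) on risk of VTE, CVA and risk of revision". Mortality is not among those outcomes.
- **Available data.** The opening paragraph says the registry holds variables "known to affect mortality, implant survivorship (revision rate) and the risk of VTE", and lists age, BMI and ASA grade among them. Method adds comorbidities by linkage to HES.
- **Exposure.** The Introduction states: "In the UK, over 90% of TKRs are performed with a tourniquet".

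**The concern.** Revision appears under both methods, mortality only under the unadjusted one. Followed as written, the plan gives revision a crude and an adjusted comparison, and mortality a crude comparison alone. Whether a tourniquet was used was presumably the surgeon's choice, and the untreated group is probably a small minority. The pilot's own Exclusion criteria show one way the groups could differ in prognosis: they exclude patients "not suitable for a thigh tourniquet (eg, peripheral vascular" disease). The cohort's Method states no such exclusion.

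For revision, a logistic model at a fixed horizon needs a yes or no for every patient. A patient who dies unrevised in year 4 must be counted as unrevised at 10 years or dropped, and the article states neither. Kaplan-Meier on the same outcome would ordinarily censor that patient at death. The crude and adjusted revision results would then answer different questions.

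The Conclusions section puts the cohort results before the consensus workshop, which judges whether the safety data remain insufficient and chooses a primary outcome for a full trial. Revision rates are among the named candidates.

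**Working it through.** The article gives no event rate, sample size or effect figure for the cohort, so there is no stated figure to reproduce. **Every rate below is an assumption, shown as a range.**

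**1. Unadjusted 12-month mortality, with no true tourniquet effect.** Take one binary risk factor that multiplies mortality by k, with prevalence p1 in the tourniquet group and p0 in the other. The apparent risk ratio is

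(1 + p1(k − 1)) / (1 + p0(k − 1)).

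| Assumed p1 vs p0 | k | Calculation | Apparent ratio |
|---|---|---|---|
| 2% vs 10% | 2 | 1.02 / 1.10 | 0.93 |
| 2% vs 20% | 3 | 1.04 / 1.40 | 0.74 |
| 20% vs 30% | 2 | 1.20 / 1.30 | 0.92 |
| 20% vs 40% | 4 | 1.60 / 2.20 | 0.73 |
| 20% vs 20% | any | equal | 1.00 |

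The first two rows represent an uncommon contraindication such as vascular disease. The next two represent a commoner marker such as a high ASA grade. If the risk factor were commoner in the tourniquet group, the ratio would lie above 1.

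**2. Revision by logistic regression, with equal revision hazards.** Use constant hazards r (revision) and m (death). Cumulative incidence is

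CIF(t) = r/(r + m) × (1 − exp(−(r + m)t)).

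Assume net 10-year revision of 5% in both groups, and 10-year mortality of 25% with a tourniquet and 35% without.

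- r = −ln(0.95)/10 = 0.00513; m = −ln(0.75)/10 = 0.02877 and −ln(0.65)/10 = 0.04308.
- CIF at 10 years, tourniquet: 0.1513 × (1 − 0.95 × 0.75) = 0.1513 × 0.2875 = 4.35%.
- CIF at 10 years, no tourniquet: 0.1064 × (1 − 0.95 × 0.65) = 0.1064 × 0.3825 = 4.07%.
- Dead counted as unrevised: OR = (0.0435/0.9565) / (0.0407/0.9593) = 1.07.
- Dead dropped, so revised against alive and unrevised: OR = (0.0435/0.7125) / (0.0407/0.6175) = 0.93.

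The true hazard ratio is 1 throughout. By horizon:

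| 10-year mortality, tourniquet vs none | Year | OR, dead = unrevised | OR, dead dropped |
|---|---|---|---|
| 25% vs 35% | 1 | 1.01 | 0.99 |
| | 5 | 1.04 | 0.96 |
| | 10 | 1.07 | 0.93 |
| 25% vs 45% | 1 | 1.02 | 0.98 |
| | 5 | 1.08 | 0.92 |
| | 10 | 1.16 | 0.85 |
| equal | any | 1.00 | 1.00 |

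Changing net revision to 3% or 8% leaves these almost unchanged.

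**3. Smaller mortality gaps.** Carry the vascular-disease assumptions from step 1 (2% vs 10–20%, mortality hazard 2–3 times higher) to 10 years, with base mortality of 25–30% and 5% net revision. Ten-year mortality is then about 25–31% vs 27–37%, and the OR with the dead counted as unrevised is 1.01 to 1.05.

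**4. Absolute rates.** With 5% net revision and 25–35% mortality, 1 − Kaplan-Meier at 10 years is 5.0%, against cumulative incidence of 4.35% to 4.07%. This affects the reported rates. It does not create a group difference when the revision hazards are equal.

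**The case against.** Several objections have force.

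- **Condensed text.** The section is three sentences in a journal article, and mortality may have dropped out of the regression list by abbreviation. But the article does not simply stay silent: it assigns mortality to one method and lists the outcomes of the other.
- **Length of stay and complications.** A reader might infer that these will go unadjusted too. No method at all is named for them, and the full protocol or analysis plan may supply one. That is no finding.
- **Stroke.** A reader might extend the confounding argument to CVA. The documents do not support this: CVA is in the adjusted model, and comorbidities are among its covariates.
- **Death coding.** A reader might infer that the logistic model counts the dead as never revised. The article does not say so, and step 2 shows the direction reverses if they are dropped.
- **The odds ratios above are unadjusted.** The planned model includes age, ASA grade and comorbidities, the likely drivers of unequal mortality. Only a difference remaining after adjustment could distort the contrast, so the figures in step 2 are not the bias of the planned model. Step 3 shows that more modest assumptions give even less.
- **Length of follow-up.** The operations date from April to December 2003, so ten years had passed by December 2013, before the ethics approval of January 2016. Administrative censoring need not arise, and death is the main reason for incomplete follow-up.
- **Kaplan-Meier and Cox also censor deaths.** True. For comparing revision rates this is acceptable, and with equal hazards both show no difference. For absolute risk it is not enough, which is why cumulative incidence is needed as well.

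What stands is the crude mortality contrast, and the choice of a model without event times for revision at 5 and 10 years.

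**Conclusion.** The point holds in two parts, at moderate severity.

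**Mortality.** As written, the only comparison is unadjusted, although the exposure is not randomised and adjustment variables are available. It may be confounded. The range of 0.73 to 0.93 rests on assumed imbalances that make the no-tourniquet group the sicker one; with balanced groups the ratio is 1.00. A reader might conclude that the contrast *is* confounded, or that it will flatter tourniquets. The documents give no distribution of risk factors by group, so neither follows. The planned baseline comparison would help to reveal an imbalance but would not correct for it.

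**Revision.** Logistic regression is nearly harmless at 1 year (within about 2% under the assumptions used). At 10 years the illustrated departure is about 1% to 16% and needs unequal mortality. How much would survive the planned adjustment is unknown.

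The cohort is supporting evidence, presented beside the pilot trial and published data. No feasibility criterion sets a registry mortality threshold, and mortality is not among the primary outcomes named as examples there. This should be corrected, but it does not undermine the study.

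**What to change.** 1. Add 12-month all-cause mortality to the adjusted analyses, by Cox or logistic regression, with the covariates already listed in the cohort's Statistical Analysis section. Keep the Kaplan-Meier curves as description.
2. For revision, replace logistic regression with an adjusted cause-specific Cox model. Report cumulative incidence at 1, 5 and 10 years by group, with death as a competing event.

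When reusing the covariate list, settle two details: sex is named in Method but not in the list, and a cemented/uncemented term cannot vary when only cemented replacements are analysed.

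The cost is a few extra models. Registry and linked HES data are already requested, and mortality and revision times are needed for the planned Kaplan-Meier curves anyway. No new data collection follows.

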There may be problems with running a trial that involves recruiting patients who,
once it is explained, may not be prepared to accept the potential risks of surgery
with a tourniquet. Equally, surgeons may be not willing to change surgical practice
for a randomised trial.

We designed a feasibility study, which includes three separate but integrated
projects: (A) pilot randomised controlled trial (RCT), (B) integrated qualitative
research study and (C) retrospective multicentre cohort study.

The objective of the safety and feasiblity evaluation of tourniquets for total knee
replacement surgery (SAFE-TKR) study is to establish whether a full
RCT evaluating tourniquets in knee replacement surgery is warranted and
feasible.

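### The cohort's regression model lists no surgeon, hospital or provider-sector term, so the standard error for the tourniquet effect may be too small and provider differences are left unadjusted

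*Protocol article*

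**What the plan says.** The Statistical Analysis section of the Multicentre cohort study names a "Multivariate logistic" model for VTE, stroke and revision, and it lists the terms. In its words, "regression will be used to assess the effect of age, BMI, socioeconomic status", and the list continues with "tourniquet use, type of VTE prophylaxis, ASA grade, comorbidities and type of" TKR implant. Apart from tourniquet use itself, these are patient, prophylaxis or implant variables. For time-to-event summaries, "The Kaplan-Meier method will be used to calculate mortality and revision rates in" the two tourniquet groups. No random effect, cluster-robust standard error or stratification is mentioned for either analysis.

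The section introducing the cohort describes the source. The registry listed 406 hospitals from the NHS, the independent sector and treatment centres, "and of these, 384 returned data". The baseline variables to be compared between groups, listed in the cohort's Method section, also include no hospital, surgeon or sector item.

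On who decides about the tourniquet, the Introduction says "In the UK, over 90% of TKRs are performed with a tourniquet", explains its use by what surgeons believe about operative view and cementation, and warns that "surgeons may be not willing to change surgical practice" for a randomised trial. The qualitative study samples surgeons by whether they are in equipoise, and the feasibility criteria ask whether surgeons are prepared to operate either way.

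**The concern.** Where an exposure is chosen mainly by the surgeon or the unit, patients of the same surgeon share both the exposure and whatever else that surgeon or unit contributes to outcome. A patient-level logistic model with ordinary standard errors then counts more independent information about the tourniquet coefficient than the data hold. Because fewer than 10% of operations are expected to be without a tourniquet, the comparison group may also come from relatively few units.

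Provider type is a second, separate matter. If non-use were more common in one sector, and outcomes differed by sector for other reasons, the stated covariates would not fully remove that difference.

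The results go to the consensus workshop. One of its criteria is whether the data on safety and effectiveness remain insufficient, which is partly a judgement about precision. The Conclusions section also allows pooling of the pilot, the cohort and published data. An understated standard error would give the cohort estimate too much weight there.

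**Working it through.** **The plan's own figure.** 384/406 = 94.6%. The article states 94%, which is the same figure truncated; nothing turns on this. No sample size, precision or power is stated for the cohort.

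**Inputs from the article.** 384 hospitals of mixed type; tourniquet use above 90%; a logistic model with a closed covariate list.

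**Inputs assumed, because the article gives none.** Cluster size m; outcome intracluster correlation ρ; and the degree to which tourniquet use itself clusters, ρx (1 = fixed within cluster, 0 = fully mixed).

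**Formulae.** Design effect DE = 1 + (m − 1)·ρ·ρx. Ratio of correct to ordinary standard error = √DE. Actual coverage of a nominal 95% interval = 2Φ(1.96/√DE) − 1.

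**Use constant within cluster (ρx = 1).**
- m = 30, ρ = 0.01: DE = 1 + 29 × 0.01 = 1.29; ratio 1.14; coverage about 92%.
- m = 30, ρ = 0.05: DE = 1 + 29 × 0.05 = 2.45; ratio 1.57; coverage about 79%.
- m = 50, ρ = 0.01: DE = 1 + 49 × 0.01 = 1.49; ratio 1.22; coverage 89.2%.
- m = 50, ρ = 0.05: DE = 1 + 49 × 0.05 = 3.45; ratio 1.86; coverage 70.9%.

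**Where the loss shrinks.**
- m = 10, ρ = 0.005, ρx = 1: DE = 1 + 9 × 0.005 = 1.045; ratio 1.02.
- m = 20, ρ = 0.001, ρx = 1: DE = 1.02; ratio 1.01; coverage 94.8%.
- m = 50, ρ = 0.01, ρx = 0.5: DE = 1 + 49 × 0.01 × 0.5 = 1.25; ratio 1.12; coverage 92.1%.
- ρx = 0: DE = 1.00, no loss.

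**Simulation check.** 384 clusters of 50, 2% event rate, 90% exposed, no true effect, unadjusted log odds ratio with ordinary standard error, 2,000 runs per setting.

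| Between-cluster SD (log odds) | Coverage, use fixed by cluster | Coverage, use mixed within cluster |
|---|---|---|
| 0 | 95.5% | 95.2% |
| 0.3 | 94.9% | 94.7% |
| 0.5 | 91.3% | 94.7% |
| 0.8 | 84.1% | 94.6% |

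The mean log odds ratio stayed between 0.004 and 0.017 throughout. Clustering alone therefore affects the standard error, not the estimate.

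**Effect on pooling.** Under inverse-variance weighting, an uncorrected variance overstates the cohort's weight by the factor DE: 1.29 to 3.45 over the main range above.

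**The case against.** The best defence is that the section is silent on variance estimation. A logistic model is compatible with cluster-robust errors, and a condensed article often leaves such detail to the full protocol or analysis plan. This stands in part: one cannot say that independence is declared. But the article does give the adjustment set, and sector and hospital are absent from it although the mix of providers is described in the same part of the article. That is a stated choice, not an omitted detail.

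Several stronger readings are tempting and are not supported:

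- *That tourniquet use is a fixed surgeon habit.* A national proportion above 90% says nothing about variation within a surgeon. The remark on unwillingness to change is a conditional worry about joining a trial. The pilot's exclusion of patients unsuited to a thigh tourniquet shows that non-use can also be a patient-level decision. Clustering by surgeon is a plausible reading and is not quantified.
- *That the intervals are too narrow as a matter of fact.* The shortfall depends on three unknown quantities and can be nil.
- *That surgeon or hospital differences will be read as tourniquet effects.* Bias needs unit-level outcome to be related to tourniquet use. No section shows that or excludes it.
- *That the no-tourniquet group is worth only as many observations as it has surgeons.* That is the limit at ρ = 1. At m = 30, a cluster still supplies 30/1.29 ≈ 23 to 30/2.45 ≈ 12 effective patients; at m = 50, 50/1.49 ≈ 34 to 50/3.45 ≈ 14.

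The cohort is also not confirmatory and is one of several inputs to the workshop, which limits the consequence.

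**Conclusion.** The point holds in conditional form. The listed model has no surgeon, hospital or provider-sector term, while the data come from 384 hospitals of mixed type and the exposure plausibly follows the surgeon. Run as written with ordinary standard errors, it understates uncertainty about the tourniquet effect to the extent that use and outcome both cluster. The correct standard errors would be about 1.14 to 1.86 times larger if use is constant within clusters of 30 to 50 and ρ is 0.01 to 0.05. All of these inputs are assumptions. The loss is negligible for small clusters with very small ρ, and absent if use is fully mixed within clusters. Lack of adjustment for provider type is possible confounding only. The change is worth making because it is cheap and because the workshop's question turns partly on precision.

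**What to change.** In the Statistical Analysis section of the Multicentre cohort study:

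1. Compute the tourniquet contrasts with standard errors clustered on hospital, or on surgeon if surgeon codes are available. The article does not show that surgeon codes are in the extract. Clustering on hospital also covers surgeons who operate within a single hospital.
2. Add provider sector (NHS, independent, treatment centre) as a covariate. A hospital random intercept is not a substitute: it assumes unit effects unrelated to exposure, so by itself it does not remove confounding by unit.
3. Beside each estimate, report how many hospitals (and surgeons, if known) contribute no-tourniquet cases. If that number is small, cluster-robust errors are themselves unreliable and the reader should know it.

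The cost is a few lines of analysis text, possibly a request for an extra data field, slightly more analysis work and wider intervals. If use proves to be mixed within units, the intervals will barely change.

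### The registry model's implant covariate is constant in a cemented-only cohort, so it gives no adjustment for implant type; the same model omits the sex term promised for revision

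*Protocol article*

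**What the plan says.** All references are to the Multicentre cohort study in the protocol article.

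- **Introductory paragraph.** Among the National Joint Registry (NJR) variables said to be known to affect mortality, implant survival and VTE risk, it numbers "2) type of implant used, (3) use of" cement as two separate items.
- **Method, cohort.** "We will analyse only data from primary cemented TKRs". The same section includes implant type among the baseline characteristics to be compared between the tourniquet and no-tourniquet groups.
- **Method, revision.** Tourniquet use is to be analysed together with age at "time of surgery, sex and ASA classification", in order to "measure for independent effects on all cause revision".
- **Statistical Analysis.** The logistic model's covariate list starts with age, BMI and socioeconomic status, goes on to tourniquet use, VTE prophylaxis, ASA grade and comorbidities, and ends with the implant term, worded as "TKR implant (cemented or uncemented) on risk of VTE, CVA and risk of revision". Sex does not appear. The Kaplan-Meier mortality and revision rates in the same section are not described as adjusted.

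**The concern.** Two explicit statements in adjacent sections cannot both hold. If every knee is cemented, a covariate that separates cemented from uncemented knees carries no information. The parenthesis in the model defines implant type as cement status, so the one term that could have adjusted for implant type becomes a constant. The Method meanwhile expects implant type to vary within the cemented cohort, since it is to be compared between groups there.

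Sex has a similar mismatch. The Method commits to it for revision, and the model for revision leaves it out.

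Tourniquet use in the 2003 registry data was not randomised, and the logistic model is the only control of confounding that the article describes. The results matter to the programme: "The results of these analyses will inform the planning of a subsequent" definitive trial, and the cohort findings go to the closing consensus workshop. VTE and revision, both outcomes of this model, are among the candidate primary outcomes for the full trial.

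**Working it through.** The article gives no sample size, effect size or event rate for this cohort, so there is no figure to reproduce. The check compares the sections and then works out what a constant covariate does to the model.

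**1. Count the model terms.** Statistical Analysis lists: (1) age, (2) BMI, (3) socioeconomic status, (4) tourniquet use, (5) type of VTE prophylaxis, (6) ASA grade, (7) comorbidities, (8) implant type, glossed as cemented or uncemented. That is eight terms. Sex is not one of them, and socioeconomic status cannot be read as including it.

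**2. Apply the cohort restriction.** Let C = 1 for cemented and 0 for uncemented. Under the Method, C = 1 for every patient. The linear predictor is

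logit(p) = b0 + bC·C + (the other seven terms) = (b0 + bC) + (the other seven terms).

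Only the sum b0 + bC is identified. So bC has no estimate for VTE, CVA or revision, and the other seven coefficients are the same whether C is kept or dropped.

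**3. Numerical confirmation on simulated data.** Assumed inputs, not from the article: 20,000 patients; age with mean 70 and SD 9; ASA grades 1 to 3; 90% with a tourniquet; C = 1 throughout.

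| Quantity | With C | Without C |
|---|---|---|
| Columns in design matrix | 5 | 4 |
| Rank | 4 | 4 |
| Tourniquet coefficient | 0.0388 | 0.0388 |
| Intercept (plus bC where present) | -1.863 + (-1.863) = -3.726 | -3.726 |

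The age and ASA coefficients also agree between the fits. The coefficient values come from one simulated draw and say nothing about tourniquets; only their equality matters.

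**4. Set the two descriptions of implant type side by side.** The introductory paragraph has implant type and cement use as two variables. Restricting to cemented knees deals with cement use by design. It does nothing for the other features of the implant, and the model as printed has no term for them.

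**5. Compare the sex statements by outcome.**

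| Outcome | Method commits to sex? | In the model list? |
|---|---|---|
| All-cause revision | Yes | No |
| VTE | No explicit commitment | No |
| CVA | No explicit commitment | No |

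Only the revision row is a contradiction.

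**The case against.** The best defence is that little is damaged. Software will drop the constant, the tourniquet estimate will not move, and the model still adjusts for age, BMI, socioeconomic status, VTE prophylaxis, ASA grade and comorbidities. Cement use itself cannot confound in a cohort where everyone has cement. All of this stands. A reader might infer that the registry adjustment as a whole cannot be carried out; the article does not support that, because only one of the eight terms fails.

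A second defence is that the parenthesis is a careless gloss and that the registry's implant-type variable was always meant, as its place in the baseline comparison suggests. That may be so, and nothing in the article shows a decision to leave implant type out. But the printed model still defines the term as cement status, and an analyst who follows it gets no adjustment for implant type.

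A third is that the Method already commits to sex for revision and that a condensed article need not repeat every covariate for each outcome. The first half is true, and it is why the omission is a contradiction. The second half would excuse a missing list, but here a list is given and it conflicts with the Method. A reader might go further and conclude that sex was intended for VTE and CVA too. The article makes no such commitment, and sex is not named among the variables that the introductory paragraph says affect outcome.

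**Conclusion.** The point holds at moderate severity. Following the printed model, one term in eight is void, implant type goes unadjusted in all three outcome models, and sex goes unadjusted in the revision model despite the Method's statement. The rest of the model, including the tourniquet coefficient, can be fitted.

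The size and direction of any bias cannot be determined. They depend on how implant type and sex relate both to tourniquet use and to each outcome, given the other covariates, and the article gives neither. It would be tempting to say that bias is absent only if both variables are balanced between the groups. That is too strong, since a variable with no effect on the outcome given the other covariates does not confound even when it is unbalanced.

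A more severe rating is not warranted. This is an observational component of a feasibility study, one of several inputs to the workshop, and it does not bear on the pilot trial's primary objective of estimating recruitment, crossover and follow-up. The conclusion assumes that the cohort restriction and the covariate list both mean what they say; a fuller plan, not shown, may already resolve the conflict.

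**What to change.** Reconcile the Method and Statistical Analysis sections of the cohort study:

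1. Keep the cemented-only restriction and replace the cemented/uncemented term with the NJR implant-type variable that the article already names. If uncemented knees are in fact wanted, remove the restriction from the Method instead and keep cement use and implant type as separate covariates.
2. Add sex to the revision model, as the Method promises.
3. Optionally, add sex to the VTE and CVA models. This is an improvement, not the repair of a contradiction.

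The cost under the cemented-only option is about one sentence of text and no new data: the Method calls sex a routinely collected NJR variable, and implant type is in the same dataset. Admitting uncemented knees would also change the analysis population.
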